### Patient and public involvement

Patients are not participants in this study. Patients attending appointments in the participating GP practices will be informed of the study by letter/email/text message. They can then opt out of having their data used in the study by informing their GP practice or the research team.

A patient public involvement (PPI) group of five members was recruited via VOCAL, a local Manchester organisation, which connects people with research studies. The PPI was convened during the initial planning phase. The members of the group comprise two men and three women who reside in the NHS Greater Manchester health board. They range in age, physical ability, ethnicity and diabetes type. The PPI group reviewed the clinician-facing system during interface development, and their concerns and suggestions were incorporated into the system and protocol design. The PPI group also reviewed the patient-facing letter and co-designed the poster and leaflet. Finally, the group will be asked to co-design and review study dissemination materials. In addition, one patient representative serves on the study board.

### Inclusion

All participants will be 18 years or over, able to provide informed consent and not be employed by MWDH, involved in design and development or an employee or paid consultant for any marketing research company, national regulatory agency or medical device manufacturer.

Clinician participants will be qualified HCPs (GP or RN) involved in the care of people with diabetes within NHS Greater Manchester.

Validator participants will be diabetes specialists with appropriate medical qualifications (eg, general medical council certificate of completion of training).

### Exclusion

Clinicians who do not meet the inclusion criteria.

### Data collection

The study objectives will be assessed through a range of triangulated qualitative and quantitative methods. First, pseudonymised routinely collected clinical data will be collected for quantitative analysis. This will provide an overview of the diabetes population served by the clinician participants (see tables1  2).

**Table 1 T1:** Primary outcome linked to methods for MyWay intelligence quotient testing

Primary outcomes linked to methods for MWIQ testing			
**PRIMARY OUTCOME**	**DESCRIPTION**	**METHODS**	**MEASURES TO BE EMPLOYED**
System safety	Identify and mitigate risks in the MWIQ system through a systematic evaluation of the platform’s safety in clinical settings	Weekly questionnaires End-of-study questionnaires Unsolicited issues highlighted by participants	Number of risks identified by patient-level questionnaires (interim and cumulative total), expressed as a percentage (and binomial proportion CI) of number of the patient records reviewed Clinical safety score recorded within the weekly questionnaire for each of the MWIQ features (diabetes subtype predictor, diabetes drug response predictor and diabetes complications predictor), as well as overall experience. This score will be recorded via a 5-point Likert scale, and the distribution of scores will be expressed as a percentage of responses received Clinical plausibility score recorded within the weekly questionnaire for each of the MWIQ features (diabetes subtype predictor, diabetes drug response predictor and diabetes complications predictor) as well as overall experience. The score will be recorded via a 5-point Likert scale, and the distribution of scores will be expressed as a percentage of responses received Free-text comments will be analysed for emergent themes

MWIQ, MyWay intelligence quotient.

**Table 2 T2:** Secondary outcomes and the method of testing for MyWay intelligence quotient testing

Secondary outcomes linked to methods for MWIQ testing		
**SECONDARY OUTCOMES**	**METHODS**	**MEASURES TO BE EMPLOYED**
Clinical impact	Routinely collected clinical data System navigation data Weekly questionnaire data	Number of patients with the following care processes recorded within the past 12 months: HbA1c, blood pressure (BP), serum cholesterol, serum creatinine, urinary albumin, foot screening, body mass index and smoking status. Each will be expressed as a percentage of the total number of people with diabetes seen by participants within the study period (and binomial proportion CI). Analysis will be stratified in accordance with diabetes type, age, gender, ethnicity and socioeconomic status (derived via the English index of multiple deprivation score) Number of patients meeting the following treatment targets: HbA1c <58 mmol/mol, BP=<140/80 mm Hg, Cholesterol <5 mmol/L, as well as the number meeting all three targets. Each will be expressed as a percentage of the total number of people with diabetes seen by participants within the study period (and binomial proportion CI) Number of patients with reclassified diabetes diagnosis, expressed as a percentage of the total number of people with diabetes seen by participants within the study period (and binomial proportion CI) and calculated on a monthly basis to demonstrate secular trends (if any) Number of patients with a modification in number of/dose/type of diabetes-related prescriptions (ie, insulin, metformin, DPP-4 inhibitors, pioglitazone, sulphonylurea and/or SLGT2-inhibitors) expressed as a percentage of the total number of people with diabetes seen by participants within the study period, calculated on a monthly basis to demonstrate secular trends (if any). Subjective assessment of system impact—recorded via a 5-point Likert scale. The distribution of scores will be expressed as a percentage of responses received Free-text comments submitted via questionnaire were analysed for emergent themes Number of participant interactions with the system, time spent within the system (cumulative total and per patient)
System appropriateness/applicability	Weekly questionnaires Semi-structured interviews	Clinical usefulness score recorded within weekly questionnaire for each of the MWIQ features (diabetes subtype predictor, diabetes drug response predictor and diabetes complications predictor) as well as overall experience. The score will be recorded via a 5-point Likert scale, and the distribution of scores will be expressed as a percentage of responses received Free-text comments will be analysed for emergent themes
System usability	Weekly system usability scale questionnaires End of study system Usability scale questionnaires Semi-structured interviews	Overall ease of use, recorded via a 5-point Likert scale. The distribution of scores will be expressed as a percentage of responses received Free-text comments and semi-structured interviews will be analysed for emergent themes

MWIQ, MyWay intelligence quotient.

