In addition, four validator participants will be recruited to review the patient data for safety issues. The validator participants will review the case records of all people with diabetes registered within the participating practice in advance of (and following) a scheduled diabetes review in the participating practice. Validation will consider the safety, applicability and usefulness of the system outputs. Any safety concerns will be flagged and investigated, and clinical participants will be advised not to access the patient record until the issue is resolved. Confidential advisory group approval has been granted to enable clinical validators to access relevant patient records in the participating clinics.

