## Testing protocol

Clinical participants attend an information session and provide written informed consent to the study team before being trained in the use of the system. No additional software is required to access the MWIQ system, and the validators and clinician participants do not require any additional expertise to operate the system. Validators and clinician participants are given an online link before they start testing. Once signed into the system, they can review a patient’s record. Only clinician participants can input any additional clinical data, for example, test results or changes in smoking status, to generate outputs from the system. The system will not generate an output if there is insufficient clinical data input.

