### Ensuring safety during testing

Prior to the system going live within primary care, Validator participants will review real-world patient data in the context of a ‘simulated clinic’. Feedback will be sought on system performance, usability and any identifiable potential risks. The results of this ‘simulated clinic’ testing will be provided to and reviewed by a data and safety monitoring board (DSMB), which is composed of three diabetes experts. They will make a go/no-go decision on proceeding with the study. The DSMB will meet monthly for the duration of the study to review emergent data. Ongoing data collection is subject to their review.

Safety will be ensured and evaluated by:

The clinician participants will be trained to use the MW IQ system before testing commences.Clinicians will exercise their usual clinical judgement with each patient.Validator participants will review the patient data and submit an assessment report for each person seen by the clinician participants pre-consultation and postconsultation (figure 3).Clinician participants provide review through weekly questionnaires and interviews.A yellow card-type system will be in operation for reporting urgent safety issues.Any flagged safety issues and their reports will be collated and reviewed by the MYIQ clinical team. They will then be submitted to the study DSMB).Pass/fail criteria to be applied to the result of the clinical investigation, and the DSMB will consider safety data before determining whether to proceed.

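### The first primary safety measure puts a binomial confidence interval on a count of risks per record, which is not a binomial proportion unless each record can carry at most one risk

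*Protocol article*

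**What the plan says.** Table 1 (Data collection) lists several measures for system safety. The first is the "Number of risks identified by patient-level questionnaires (interim and cumulative total), expressed as a percentage (and binomial proportion CI"); the denominator is the count of patient records reviewed. This fixes the numerator, the denominator and the type of interval.

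Four other statements bear on it:

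- Study design: "four validator participants will be recruited to review the patient data for safety issues", and the review is made in advance of, and following, a scheduled diabetes review.
- Ensuring safety during testing: validators "submit an assessment report for each person seen by the clinician participants pre-consultation and postconsultation".
- Quantitative data collection: the validation questionnaire for each patient records whether the review was made before or after the consultation.
- Testing protocol: "The system will not generate an output if there is insufficient clinical data input".

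Table 2 is built differently. Its measures with a binomial interval (care processes, treatment targets, reclassified diagnosis) all count patients over people with diabetes seen.

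**The concern.** A binomial interval needs one yes-or-no result per unit of the denominator. Table 1 instead divides a number of risks by a number of records. If one record can contribute two or three risks, the result is a rate. Its variance depends on how risks bunch within records, and the binomial formula takes no account of that.

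Two features make multiple risks per record plausible. The system has three predictor tools, any of which could give a questionable output for the same person. And each person is assessed twice, so one problem may be recorded twice. The article also leaves open whether a record reviewed is a patient or a single review.

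At stake is the stated precision of a primary safety measure in a study meant to support a regulatory submission. An interval that is too narrow would make the risk frequency look better known than it is.

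**Working it through.** **Figure to reproduce.** None. The article gives no expected value, precision target or threshold for this measure.

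**Inputs.** n = 665, the approximate number of people expected to attend for a diabetes check (Study design). The article does not tie this number to the measure; it serves here as a realistic size. The share of records flagged (p) and the number of risks per flagged record are assumptions.

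**Step 1: range.** 700 risks in 665 records give 700/665 = 105%. No binomial interval exists. An exact Poisson interval for the rate does: 97.6 to 113.4 per 100 records.

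**Step 2: variance.** Assume a record is flagged with probability p and then carries 1, 2 or 3 risks with equal chance.

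- Mean risks per record = 2p.
- True variance per record = p × (1 + 4 + 9)/3 − (2p)² = 4.667p − 4p².
- Variance the binomial formula assumes = 2p(1 − 2p).

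| p | True variance | Binomial variance | Ratio | Standard error too small by factor |
|---|---|---|---|---|
| 0.05 | 0.223 | 0.090 | 2.48 | 1.58 |
| 0.10 | 0.427 | 0.160 | 2.67 | 1.63 |
| 0.20 | 0.773 | 0.240 | 3.22 | 1.80 |

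A normal approximation then gives coverage P(|Z| < 1.96/factor) of about 79%, 77% and 73%.

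**Step 3: simulated coverage.** Exact (Clopper–Pearson) 95% interval, 20,000 runs per cell:

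| Assumption | p = 0.05 | p = 0.10 | p = 0.20 |
|---|---|---|---|
| At most one risk per record | 95.9% | 95.6% | 95.8% |
| 1 to 3 risks per flagged record | 79.8% | 78.5% | 73.7% |
| Same risk counted before and after, denominator 665 | 84.4% | 80.7% | 77.7% |
| Same risk counted before and after, denominator 1,330 | 84.5% | 84.8% | 84.2% |

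The second row agrees with Step 2. The first row shows that the interval works once each independent record yields a single 0/1 result.

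**Step 4: low counts.** Seven risks in seven different records of 665 give 1.05%, binomial 0.42–2.16% and Poisson 0.42–2.17%. With few events and no multiples the choice hardly matters.

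**Step 5: unit of review.** If 33 risks are counted, 33/665 = 5.0% per patient and 33/1,330 = 2.5% per review. The article does not say which is meant.

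**Step 6: records without output.** Suppose 33 records carry a risk and all of them have an output. With all records as denominator, 33/665 = 5.0%. Restricted to records with an output, the figure is 33/598 = 5.5% if 10% have none, 33/532 = 6.2% if 20%, 33/465 = 7.1% if 30%, and 33/332 = 9.9% if 50%. These shares are assumptions; the article gives none.

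**The case against.** The strongest reply is that the article calls its quantitative analysis descriptive and ties no threshold to this percentage. Pass/fail criteria and monthly review by the monitoring board are mentioned, but neither is linked to this figure. Risks per 100 records is also a sensible description for a study meant to find and reduce risks. This stands, and it limits the severity. It does not rescue the interval: the article chose to specify one, and it should match its quantity.

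A second reply is that several risks per record are possible but not shown. The validation questionnaire is described as holding the review timing and comments, not a tally by tool, and the scores "for each of the MWIQ features (diabetes subtype predictor, diabetes drug response predictor and diabetes complications predictor") come from the weekly questionnaire. This too is fair. If the form allows only one risk per patient, the interval is right. The text does not say so.

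Three stronger readings are tempting but unsupported:

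- **That records without output dilute the risk figure.** The article says "The validator participants will review the case records of all people with diabetes registered within the participating practice" around scheduled reviews, with no output condition, but it never says whether records without output stay in this denominator. Keeping them would be a choice, not a statistical error, and failure to give an output could itself be recorded as a risk.
- **That pre- and post-consultation reviews are pooled, or that the later set is filtered.** Pooling is not stated. On flagged records the article says "clinical participants will be advised not to access the patient record until the issue is resolved", which is a temporary hold; nothing removes them from later review.
- **That the safety figure as a whole is invalid, or makes the system look too safe.** The count and the rate are legitimate descriptions, other measures stand beside this one, and counting several risks per record raises the figure.

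Finally, an article may leave the unit of review to the full protocol. That applies to the unit, but not to the mismatch, because Table 1 itself fixes numerator, denominator and interval.

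**Conclusion.** The point holds in a limited form. As specified, the measure is a rate of risks per record carrying an interval meant for a proportion. At 665 records and 5–20% flagged, the nominal 95% interval covers about 74–80% if flagged records carry 1 to 3 risks, and about 78–85% if each risk is counted at both reviews. Both patterns are assumptions. With at most one risk per record, coverage is 95.6–95.9% and there is no problem.

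That last result also assumes independent records. Four validators may differ in how readily they flag: with an assumed intraclass correlation of 0.01 and 166 records each, coverage falls to about 78–79% even with one risk per record. Redefining the numerator does not remove this, so it should be acknowledged when the interval is reported.

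Severity is moderate: the measure is primary, but the analysis is declared descriptive and no decision rule is attached to this percentage.

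**What to change.** Reword the first measure in Table 1, and the matching text in the full protocol or analysis plan:

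1. **Measure:** the number of unique patient records with at least one risk, divided by unique patient records reviewed, with the binomial interval. Show pre- and post-consultation findings separately, using the timing field already on the validation form.
2. **Alongside it:** the total number of risks as a rate per 100 records, with an interval that allows for several risks per record, such as an overdispersion-robust or patient-level bootstrap interval.
3. **As secondary description:** the share of reviewed records with no system output, and the percentage with a risk among records that had one.

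The main measure should not be confined to pre-consultation records with an output, because risks first found after the consultation would then drop out of it.

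The cost is a change of wording and a little more analysis and reporting. Item 3 also needs a record of whether an output was produced.

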### MyWay intelligence quotient (MWIQ)

MWIQ V.1.1 is an online electronic platform that provides clinical decision support around the diagnosis and treatment of patients with diabetes and will be delivered as part of the MyWay clinical and MyWay diabetes patient-facing platforms. The MWIQ clinician interface tool contains ~70 predictive models, generated through machine learning techniques and developed by MyWay digital health (MWDH). These models will be operationalised to predict glycaemic/metabolic response to type 2 diabetes pharmacological treatments, diagnosis of rare diabetes subtypes and risk of diabetes-related complications. In addition, they will provide a clinical overview of patient populations.

MWIQ machine learning models were developed through validated literature-based models, then the development of meta-models derived from them and the creation of de-novo models.

The validated literature and meta-models development predict diabetes subtype, diabetes acute and a large range of chronic complications, including cardiovascular disease, renal complications, amputation, blindness, hypoglycaemia, hospitalisation, re-hospitalisation, mortality, etc, and response to lifestyle interventions. The drug response prediction uses multi-dimensional time series data to predict the likely response to defined medications (counterfactual conditions) in domains of interest (HbA1c, blood pressure (BP), etc). Predicted outcomes guide individual therapeutic choice.

MWIQ will provide clear guideline-linked evidence-based decision support, particularly helping primary care staff who may lack specialist knowledge, by building on basic rule-based decision support, which has previously been shown to improve compliance with the guidelines by around 3–4 fold.^17^ Another important feature of the MWIQ system is the human factors approach, which is built into the development and research from the start.^18^

MWIQ aims to improve adherence to existing guidelines, while providing tailored treatment and diagnostic recommendations (within these existing guidelines) to improve future clinical outcomes (figures1  2). MWIQ is not intended to replace the care provided by licensed healthcare professionals (HCPs), involving prescribing, diagnosis or treatment. The system is supportive and advisory. Any treatment decision ultimately requires clinical judgement, taking the full clinical scenario into consideration.

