## Methods

### Study design

This study is an open-label, single-arm, mixed-methods feasibility testing of a support and decision-aid clinician-facing platform. Real-world testing will take place within the integrated care board, NHS Greater Manchester (the single site), with four to seven general practitioner (GP) surgeries participating across this large multicultural British city. The study contacted all practices within this area, and five practices responded positively. The study started recruitment for clinical participants on 28/08/2024. Live clinical testing started in March 2025, and the end of the study is 08/09/2025. Each participating practice serves a population of approximately 285 diabetes patients. Therefore, within the study period, it is anticipated that ~665 people with diabetes will attend their primary care practice for a diabetes check.

We will recruit one or two clinician participants from each of 5 GP practices, for a maximum of 10, to ensure the device is used in a variety of diabetes-related clinical settings and comprises a broad range of age groups, ethnicities and medical needs. Clinician participants will be members of the multidisciplinary team (GPs, specialist registered nurses (RNs) and advanced nurse prescribers who regularly see people with diabetes as part of their day-to-day work. They will provide a real-world perspective on how well the system integrates within the normal clinical workflow and provide feedback on how well the system performs. Sample size is calculated to withstand a small number of dropouts, while being large enough to draw out user views with different qualitative and quantitative methods and detect any safety issues across the long term. Each clinician participant will be invited to interview across the testing period (up to a maximum of 10 interviews). This is based on the narrow and focused scope of the interviews, collecting rich interview data by continuous interviewing throughout the study and the variety of HCPs involved in diabetes care in the primary sector and the anticipated number to reach data saturation for this type of study.

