### Quantitative data collection

Quantitative data will be extracted from the MyWay server and pseudonymised prior to secure file transfer to the research team. These pseudonymised data will provide an overview of the diabetes population served by the clinician participants. Data collected will include adherence to quality performance indicators, diabetes diagnosis (ie, diabetes type) and diabetes investigations (eg, genetic testing). Other routinely collected clinical data of interest include HbA1c, BP, body mass index, cholesterol and foot risk score for the diabetes population concerned. The time spent by participants within the MWIQ system will also be evaluated.

Validation questionnaires for each patient include whether the record was reviewed pre-consultation or post-consultation and any comments on the validation (eg, if the medication recommendation is what they expect). Weekly ease of use questionnaires, completed by each clinical participant, ask how easy completing tasks within each tool (diagnostic subtype, medication recommendation and the complications risk) is and for any further comments.

End-of-study questionnaires will be issued to each clinical participant and will ask for a summary of their experience over the testing period using a Likert scale to assess the safety of the diagnostic sub-type, medication recommendation and complications risk tools, clinical appropriateness, clinical flow, difficulty in using the system and any recommendations. This questionnaire will incorporate the system usability scale.^19 20^

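### The first-listed primary safety measure puts a count of risks over a count of records with a binomial CI, which is valid only if each record can contribute at most one risk

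*Protocol article*

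**What the plan says.** The Data collection section, Table 1, lists system safety as the primary outcome. Its first measure is a count, defined as follows: "risks identified by patient-level questionnaires (interim and cumulative total), expressed as a percentage (and binomial proportion CI) of number of the patient records reviewed". The other Table 1 measures are Likert distributions from the weekly questionnaire and free-text themes, so this is the only primary measure expressed per patient record.

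The only form that the article describes as completed per patient is the validators' form. Quantitative data collection says: "Validation questionnaires for each patient include whether the record was reviewed pre-consultation or post-consultation". Ensuring safety during testing says that validators "submit an assessment report for each person seen by the clinician participants pre-consultation and postconsultation". Study design likewise has validators review records in advance of and following a scheduled diabetes review, considering the system's outputs (plural) for safety, applicability and usefulness. No section limits a record to one risk, says that repeat flags are merged, or says whether a record reviewed twice counts once or twice in the denominator.

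In Table 2, every measure that carries a binomial CI (care processes, treatment targets, reclassified diagnosis) counts patients over patients.

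**The concern.** A binomial interval describes a number of successes among a number of yes/no trials. Here the trials are records, so the matching numerator is records with at least one risk. Table 1 counts risks instead. If some records contribute two or more, two things follow.

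- **The estimate.** A percentage of records with a binomial CI will be read as the share of records affected. It is really the mean number of risks per record, which is larger.
- **The interval.** The binomial variance is too small for a count that can exceed one per record, so the CI is narrower than its stated level.

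Safety is the primary objective. The data and safety monitoring board reviews emergent data monthly, and the results are meant to support a regulatory submission. The contrast with Table 2 shows that the patients-over-patients form was available. The primary safety measure departs from it.

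**Working it through.** The article gives no expected value, interval width or formula for this measure, so there is no stated result to reproduce. The check is how far the binomial standard error departs from the true one when affected records carry more than one risk.

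**Inputs**
- Records, n = 665, for illustration. Study design states: "it is anticipated that ~665 people with diabetes will attend their primary care practice for a diabetes check". The ratio of standard errors below does not depend on n.
- Share of records with any risk, q = 0.05: assumption.
- Risks per affected record = 1 + Poisson(m), with mean 1 + m: assumption, taken at m = 0, 0.1, 0.5 and 1.

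**Formulas**
- Mean risks per record: μ = q(1 + m)
- True variance per record: V = q(1 + 3m + m²) − μ², since E[(1 + Poisson(m))²] = 1 + 3m + m²
- Binomial variance per record: B = μ(1 − μ)
- SE ratio = √(V/B)

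**Results**

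| m | Mean risks per affected record | μ | V | B | SE ratio | Coverage of nominal 95% Wilson CI for μ |
|---|---|---|---|---|---|---|
| 0 | 1.0 | 0.050 | 0.05 − 0.0025 = 0.0475 | 0.0475 | 1.00 | 95% |
| 0.1 | 1.1 | 0.055 | 0.0655 − 0.003025 = 0.0625 | 0.0520 | 1.10 | 93% |
| 0.5 | 1.5 | 0.075 | 0.1375 − 0.005625 = 0.1319 | 0.0694 | 1.38 | 85% |
| 1 | 2.0 | 0.100 | 0.25 − 0.01 = 0.24 | 0.09 | 1.63 | 76–77% |

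Coverage is from simulation at n = 665. The approximation 2Φ(1.96/ratio) − 1 gives 95%, 93%, 84% and 77%. At m = 1 the true SE is √(0.24/665) = 0.0190, against a binomial √(0.09/665) = 0.0116.

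**The case closest to the design.** Suppose each affected record is flagged once before and once after the consultation, and the record counts once in the denominator. Then μ = 2q, V = 4q(1 − q), B = 2q(1 − 2q), and V/B = 2(1 − q)/(1 − 2q). At q = 0.05 this is 1.90/0.90 = 2.11, an SE ratio of 1.45 and simulated coverage of 82%. At q = 0.10 it is 1.80/0.80 = 2.25, a ratio of 1.50 and coverage of 80%.

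**Effect on the estimate.** At m = 1 the measure would be about 67/665 = 10.1% (Wilson 95% CI 8.0–12.6%), while the share of records affected is about 33/665 = 5.0% (3.6–6.9%). These estimate different quantities, so the gap does not itself show that an interval is wrong. It shows how far a reader would be misled by taking one for the other.

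**Check of the remedies.** With one count per affected record, simulated coverage of the binomial interval was 94.9–95.5%. Keeping the count of risks but using the observed between-record variance gave 93.5–95.7% in all scenarios tried.

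**The case against.** The strongest reply is that the wording is loose and the intent is a yes/no flag per record. Study design speaks of concerns being flagged and of clinicians being advised not to open the patient record until the issue is resolved, which fits a record-level reading, and the choice of a binomial CI fits it too. The counting rule may stand in the full protocol or the SAP, which are not shown. On that reading the interval is valid, as the first row of the table shows. This stands as a reason not to call the interval wrong outright. It does not remove the point: the article names the numerator, denominator and interval, and an analysis that follows those words can go wrong.

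A second reply is that the analysis is limited to descriptive statistics, so no test or sample size is affected. Flagged issues also reach the monitoring board as reports, and issues are followed weekly on run charts. This stands, and it limits the severity.

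A reader might also infer several risks per record from the software: "The MWIQ clinician interface tool contains ~70 predictive models", and Table 1 names the "diabetes subtype predictor, diabetes drug response predictor and diabetes complications predictor". That support is weak. In Table 1 the three predictors belong to the weekly scores, not to the patient-level form, and the number of models describes the platform, not what validators record. The paired review before and after the consultation is the better source. If each review were a separate unit in the denominator, that duplication would ease. Correlation between the two reviews of one patient would remain, as would the possibility of several risks within one review.

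**Conclusion.** As worded, the measure is a valid proportion with a valid binomial CI only if each record contributes at most one risk. The article does not say so, and its paired reviews make more than one possible. Where that occurs, the percentage overstates the share of records affected and the interval is too narrow. At an assumed 5% of records affected, the SE is understated by a factor of 1.10 to 1.63 as the mean rises from 1.1 to 2 risks per affected record. The error vanishes at exactly one. The multiplicity is an assumption throughout, so only this range can be given.

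Stronger readings are not supported. A reader might infer that the error bars are certainly wrong, but no passage states that a record carries several risks. A reader might infer that the ratio will pass 100%. That is arithmetically possible but remote at the rates used here. Nor does any passage tie the go/no-go decision or the pass/fail criteria to this figure. The point is one that should be fixed, not one that invalidates the study.

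**What to change.** Reword the first measure in Table 1, and the matching SAP entry, as: the number of distinct patient records with at least one risk identified, as a percentage of distinct patient records reviewed, with a binomial CI. State that a record reviewed before and after the consultation counts once, or report the two stages separately, each with its own denominator.

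If the total number of risks is also wanted, report it as risks per 100 records, with a CI based on the between-record variance (robust or record-level bootstrap). List distinct system faults with the number of records each affected, without a percentage.

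The cost is small: a short change of wording and, since the forms are completed per patient, probably no new data. The downside is that the interval for the rate of risks will be wider than the binomial one.
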